### Study design

This is an open-label, household-cluster, randomized, controlled, superiority trial using a generalized, randomized, complete, block design, with the village as a block. The study arms consist of 110 novel-design houses and 440 traditional African homes.

### Intervention

The intervention consists of a novel house design. Its structure is informed by pilot studies in Magoda, Tanzania [14]. The critical components are an elevation of the sleeping area by constructing double-storey buildings and the use of shade net as cladding to optimize airflow while minimizing the entry of insects (Fig. 1). To assure timeliness in construction and identical physical characteristics of all new houses, a light gauge steel structure was chosen by the architects. The building site was selected by the house owners in discussion with the architects to address the requirements of the house owners and optimize shade throughout the day. The raised concrete foundation serves as the ground floor and can be easily cleaned. The ground floor includes a protected lockable storage area to reduce rodent infestation and to provide a feeling of security. Each of the 3 doors comes with a spring-powered closing mechanism to minimize the time that the doors stay open. The frequency of opening and closing of the door will be recorded by data loggers via sensors. The ground floor cooking area is screened to improve airflow and reduce the entry of flies. The kitchen includes a chimney to direct the flow of smoke away from the building. Rainwater is harvested in roof gutters, which drain into 2000-l PVC water tanks. The outdoor latrines are constructed within a 10-m radius of the building, using a light gauge steel system with a fly-proof, ventilated septic tank. Each house comes with a solar power system which provides electricity for light and mobile phone charging. The new homes are designed to minimize energy consumption through reduced use of concrete and optimized airflow and ventilation. By our estimates, a novel design house uses 37% less embodied carbon, 41% less embodied energy, and 70% less concrete than a more traditional African home design of similar size [18].

**Fig. 1 Fig1:**
[figure not shown]
Diagram illustrating the critical elements of the novel rural African house design

One of the requirements for a family to participate in the lottery for a house was to have space to build a new house. This building site on the land available to the future house owner was selected in discussion between the house owner and the architects taking into account any slope in the terrain and trees which can provide shade. The orientation of the building in relation to the north-south axis was determined by the architects. The ultimate position for the latrine was the result of the discussions between the house owners and the architects. Mosquito breeding sites of mosquitoes were not taken into consideration. Because the space available for construction was limited, the new house frequently replaced the earlier traditional home.

The construction of the 110 novel-design houses started at the end of 2018 and was completed in June 2021 when the houses were handed over to the new house owners. A maximum of three new houses were built in each village to minimize the risk of mosquito diversion, i.e. mosquitoes prevented from entering an intervention house being diverted to a control house and thus inflating malaria transmission in control houses. The residual mosquito diversion is unlikely to increase exposure in unprotected homes [19].

To reduce malaria and enteric and respiratory tract infections and to improve the indoor climate and safety of our latest design (Fig. 1), the following critical structural components are included:Building orientated to provide optimal shading throughout the day to keep the house cooler at night (→ indoor climate)Lightweight and durable roof with partially closed eaves to reduce the entry of malaria vectors (→ malaria, indoor climate)Facade and openings screened to reduce insect entry while assuring airflow (→ malaria, diarrhoeal diseases, indoor climate)Raised concrete ground floor which can be easily cleaned and increases hygiene and reduces the risk of enteric and soil-transmitted infections (→ diarrhoeal diseases)A screened indoor cooking area with the means to remove smoke to reduce indoor pollution (→ respiratory infections)A protected lockable storage area to reduce rodent infestations and provide a feeling of security (→ safety)Sleeping areas with bednets raised to the first floor improving airflow and comfort while reducing mosquito density (→ malaria, indoor climate)A water harvesting system which allows the collection of rainwater from the roof, filtering, and covered storage (→ diarrhoeal diseases)An outdoor fly-proof latrine (→ diarrhoeal diseases)Solar power providing electric light at night (→ safety)

#### Participant eligibility

The randomization procedure started by identifying suitable villages based on the eligibility criteria described below.

The following are the village eligibility criteria:Size: a village of about 500 people or more (about 100 households), to make sure that we would have at least five households for randomization.Accessibility: readily accessible throughout the year to assist during the construction phase and surveillance.No competing health interventions: we selected a study area without plans for new, experimental health interventions. The routine government health interventions including the distribution of ITNs continues.No power supply: lack of electricity is representative of most rural Tanzanian villages.No water supply: few rural Tanzanian villages have access to reliable water supplies.

Following the selection of 68 eligible villages, a census of 14,600 households in the 68 villages was conducted, and data on household members and household structures were collected [17]. Data were entered in tablets and subsequently uploaded, stored, and processed using the KoBo Toolbox. Eligible households were selected according to the criteria below.

The following are the household eligibility criteria:There is sufficient land on which to construct another house.At least two children under 13 years old (no lower age limit).Willing to participate in disease surveillance for 3 years.Traditional house design constructed with mud walls, thatched roof, and dirt floor.Householders had access to a pit latrine.No power supply from the grid.No piped water supplied by the municipality.

Eligible households were identified in 60 villages; therefore, participants in 60 out of 68 villages participate in the study.

### Randomization

All households meeting the eligibility criteria were invited to participate in a randomization process in the form of a village lottery. A total of 862 households were eligible to participate in a lottery to select firstly the 110 new house owners and secondly the 440 households to serve as comparison houses. The lottery was conducted during a public meeting at a central meeting place to which all villagers were invited. All households meeting the inclusion criteria were listed, and cards with the names of the household’s heads were inserted in identical envelopes. The envelopes were placed in a transparent bucket and mixed. The lottery consisted of two rounds where the winning envelope was picked by a literate school child of any age. In the first stage, two envelopes were picked out of the bucket, and the winners were offered a new house. During the second round of the lottery, eight households were randomly selected to participate in the study as comparison households. Comparison households will receive modifications of their homes such as a corrugate iron roof and water harvesting equipment after completion of the 3-year surveillance period. All study families, control and intervention, are enrolled in a health insurance scheme which assures free healthcare for the study duration. Each household meeting the eligibility criteria had an equal and fair chance of being selected to be part of the study (Fig. 2).

**Fig. 2 Fig2:**
[figure not shown]
Assembly of study households and participants

### Community engagement

A hierarchical approach to engage the study population was chosen at the earliest contact with the prospective study communities. The study team sought the advice of the district government and based on their recommendations approached the village leadership to explain the purpose and methods of the proposed study. The village leaders organized village meetings preceding census activities in the villages. Following the completion of the census, all villagers were invited to meetings to explain the purpose of the lottery described above. During the construction phase, there was regular contact with the new house owners and their neighbours. The construction team explained the activities and, where possible, asked the new house owners to participate in the construction.

Following the hand-over of the new houses, the research team realized that envy among community members who had not been allocated a novel design house was hindering study participation. In response, a multipronged community engagement plan was implemented prior to the start of active surveillance activities. A professional drama group developed plays originally meant to be enacted as village theatre. Following COVID-19-related restrictions, the script was transformed into a radio show “Samoe” with 20 episodes of 20 min each, describing the adventures of a young couple after participating in the lottery and winning a new-design home.

Due to the popularity of sports and particularly football, the research team formed a football club which participated in weekly matches in the study villages. Additional sports activities were added for all day village “bonanzas” on weekends. In conjunction with the sports days, village open-air dances were organized in-between and after sports activities. Rest periods between activities are used to introduce the research team and explain the purpose and the methods of the study.

### Clinical data collection

Each household and household members will be assigned unique study identification numbers. Clinical data will be collected at the household level from children under 13 years of age. The follow-up period is for 3 years from 2022 to 2024. Clinical data collection will comprise active and passive surveillance, annual malaria surveys and annual anthropometric surveys.

For the active case surveillance, trained research assistants will visit each child weekly and collect disease and travel history, temperature, and a rapid diagnostic test to detect *P. falciparum* infections if there is a history of fever since the last visit. A history of diarrhoea defined by 3 loose bowel movements within a 24-hour period or a bloody loose bowel movement or an acute respiratory tract infection defined as an increased respiratory rate for age and/or difficulty breathing will be elicited at each household visit. To help the family remember what happened during the week, we have designed a disease symptoms card which the head of household or any other adult in the house completes if fever, diarrhoea, or acute respiratory tract infection is observed in a study child. The research assistants will refer ill children to a healthcare facility, as needed.

Passive case detection will be conducted in all healthcare facilities serving the study population, documented in an earlier healthcare uptake/treatment-seeking behaviour study (manuscript in preparation). Study participants will be asked to identify themselves when entering the healthcare facility to benefit from the health insurance provided by the project. The staff working in the facilities will be trained on how to document the data of study participants. Research assistants will visit the health facility and electronically record the relevant information.

To detect any difference in parasite prevalence between participants in the two study arms, annual malaria surveys will be conducted. Dried blood spots (DBS) and a rapid test for malaria will be collected from all children participating in this study. This survey will be done four times throughout the 3-year study period (at the beginning, and once every year for 3 years). The DBS will be stored in freezers until processing for PCR [20, 21].

To detect any difference in growth between preschool study participants in the two study arms, anthropometric measurements (weight, height, and mid-arm circumference) will be collected at the beginning of the study and then annually.

### Microbiology

Starting in the second year of surveillance, nasal swabs will be collected from children with symptoms consistent with acute respiratory tract infections, and rectal swabs will be collected from children with diarrhoea. In addition, a swab will be collected from a child without symptoms residing in a control house. The swabs will be transported in an appropriate transport medium at ambient temperature to the study hub in Mtwara town where the specimens will be stored at − 20 °C until final processing using multiplex PCR [22]. An air sampler will be used to collect standardized air samples to detect pathogens in air samples [23].

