The novel house design evaluated in this study addresses these environmental health risks. The underlying concept for the design is derived from traditional rural Asian house designs, which are elevated and constructed of light, air-permeable materials that facilitate airflow to minimize contact with vectors [3]. A pilot study of six prototype houses carried out in Magoda, Tanzania, in 2015 found that mosquito entry was reduced by 95% in double-storey buildings and by 70% in screened single-storey buildings compared with unmodified reference houses [14]. Both single- and double-storey houses were 2.3 °C (95% CI 2.2–2.4) cooler compared with traditional houses. The observed reduction in mosquito densities and temperature suggest that double-storey screened houses could protect best against malaria by providing a barrier to mosquito entry and encouraging bednet use in the cooler indoor environment. By promoting airflow and installing chimneys that reduce indoor smoke inhalation, the risk for respiratory tract infections could be reduced. Rainwater collection systems and hygienic, fly-proof latrines could reduce the risk of diarrhoeal disease transmission.

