### Entomology

Standard CDC light traps will be used to estimate the potential exposure to malaria mosquitoes in the bedrooms of study children in 110 novel design houses and their nearest comparison house from October 2021 to December 2023. The study area will be divided into seven geographically separated clusters, six each with 16 Star homes and 16 control houses and one with 14 Star homes and 14 control houses. Each cluster will further be divided into four sub-clusters, each with eight houses: four Star homes and four nearest neighbours’ control houses. The light traps will be suspended 1 m from the ground at the foot end of a bed where a study child is. Collections will be made from one cluster each week, with a different sub-cluster sampled on four consecutive nights each week, Monday night to Thursday night. At the end of the week, all houses will be sampled in each cluster (i.e. 32 houses). The sequence in which clusters will be visited was randomly determined. The clusters will be visited in the same sequence throughout the study period, so that each cluster will be visited in a 7-week cycle. Malaria vectors collected in the study houses will be counted and compared between the intervention and control houses and then packed in the Eppendorf tubes containing silica gel and submitted to the laboratory, for further analyses. The mosquitoes will be identified by microscopy and the numbers of *An. gambiae* s.l., *An. funestus* s.l., and other species will be recorded. The presence of sporozoites will be identified using an enzyme-linked immunosorbent assay [24], and *An. gambiae* s.l. females, typed by PCR [25].

The abundance and species of domestic flies will be assessed using baited traps installed in the cooking area of selected households, outdoors, and in latrines to assess the difference in fly densities between the two study arms. The traps will be positioned on the kitchen floor, in the corner furthest from the main door. Research assistants will collect the captured flies each evening.

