##### Microbiology

Differences in the frequency of pathogens detected in symptomatic and healthy children will be used to calculate attributable fractions of pathogens and compared between intervention and control houses. Pathogens detected by air sampling will be compared between intervention and control houses.

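### Healthy comparison swabs are described only for control houses, so the novel-house attributable fractions, and their comparison between arms, are biased whenever asymptomatic carriage differs by house type

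*Protocol article*

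**What the plan says.** Three parts of the protocol article bear on this point.

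- **Methods, Microbiology.** From the second year of surveillance, "nasal swabs will be collected from children with symptoms consistent with acute respiratory tract infections", and rectal swabs are taken from children with diarrhoea. Neither rule is limited to one arm. The healthy comparator follows: "In addition, a swab will be collected from a child without symptoms residing in a control house".
- **Secondary endpoints, Microbiology.** The frequencies of "pathogens detected in symptomatic and healthy children will be used to calculate attributable fractions of pathogens", and these are to be compared between intervention and control houses.
- **Secondary objectives.** One objective is to identify the main respiratory and diarrhoeal pathogens and compare them between the arms.

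In this article a control house is a traditional house in the comparison arm. The Entomology section, for example, describes clusters, "six each with 16 Star homes and 16 control houses", where Star home is the name for the novel design house. Mitigation of bias and confounding and Difference in growth parameters use the term in the same way.

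**The concern.** A pathogen's attributable fraction contrasts how often it is found in sick children with how often it is found in healthy children who share their background exposure. If every healthy child lives in a traditional house, then for novel-house cases symptom status and house type are completely confounded. The odds ratio combines the link between pathogen and disease with any effect of the house on carriage. The cell needed to separate the two, healthy children in novel houses, is empty, so no later analysis can recover it.

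The article gives reasons to expect that background exposure may differ. Its Background section says of enteric disease: "Rainwater collection systems and hygienic, fly-proof latrines could reduce the risk of diarrhoeal disease transmission". Of respiratory disease it says: "By promoting airflow and installing chimneys that reduce indoor smoke inhalation, the risk for respiratory tract infections could be reduced". The Intervention section links the concrete floor, screening, water harvesting and latrine to diarrhoeal disease, and smoke removal to respiratory infection.

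At stake is whether a reported difference in attributable fractions between arms reflects the causes of illness or the choice of comparators.

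**Working it through.** The article gives no figure for this comparison, so there is nothing to reproduce. It also does not state a formula for the attributable fraction. The check below uses a common one and assumed prevalences.

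**Step 1: which cells are sampled**

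| | Symptomatic | Healthy |
|---|---|---|
| Control house | yes | yes |
| Novel house | yes | not described |

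The planned contrast needs all four cells.

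**Step 2: formula.** Let p be the pathogen's prevalence in cases and c its prevalence in healthy children.

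- OR = [p/(1 - p)] / [c/(1 - c)]
- AF = p × (1 - 1/OR), which simplifies to (p - c)/(1 - c)

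**Step 3: no true difference between arms.** Assumptions, none from the document: the true AF is 0.20 in both arms; case prevalence is p = c + (1 - c) × 0.20, with c the carriage in the case's own arm; control-house carriage is 10% to 40%; the novel-to-control carriage ratio is 1.0 to 0.5.

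Worked example with control carriage 0.10 and ratio 0.5, so novel carriage is 0.05:

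- Control arm: p = 0.10 + 0.90 × 0.20 = 0.28; AF = (0.28 - 0.10)/0.90 = 0.20.
- Novel arm, own background: p = 0.05 + 0.95 × 0.20 = 0.24; AF = (0.24 - 0.05)/0.95 = 0.20.
- Novel arm, control-house background: AF = (0.24 - 0.10)/0.90 = 0.156.

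Novel-arm AF when the control-house background is used (true value 0.20 throughout):

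| Carriage ratio | Control 10% | Control 20% | Control 30% | Control 40% |
|---|---|---|---|---|
| 1.0 | 0.200 | 0.200 | 0.200 | 0.200 |
| 0.85 | 0.187 | 0.170 | 0.149 | 0.120 |
| 0.7 | 0.173 | 0.140 | 0.097 | 0.040 |
| 0.5 | 0.156 | 0.100 | 0.029 | -0.067 |

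Using each arm's own healthy children returns 0.20 in both arms in every scenario. The control-arm estimate is 0.20 throughout, so every shortfall in the table would appear as a spurious difference between arms. A carriage ratio above 1 would push the novel-arm AF up instead.

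**Step 4: a true difference between arms.** Assume p = 0.30 in both arms, with carriage 0.20 in control houses and 0.10 in novel houses.

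- Control: OR = (0.30/0.70)/(0.20/0.80) = 1.714; AF = 0.125.
- Novel, own background: OR = (0.30/0.70)/(0.10/0.90) = 3.857; AF = 0.222.
- Novel, control-house background: AF = 0.125.

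The novel-arm value is too low by (0.222 - 0.125)/0.222 = 44%, and the real difference disappears.

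The same sampling rule can therefore create a false difference (step 3) or hide a real one (step 4).

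**The case against.** **Exclusive sampling is inferred.** The Methods sentence names control houses but does not rule out healthy swabs elsewhere. The endpoint wording could be read as implying healthy children in both arms. The article also condenses a fuller protocol that is not shown, and details of comparator selection are commonly left there. This stands in part: the full protocol may provide for novel-house swabs. But the article does more than stay silent. It states a source, gives no other, and that source does not serve the comparison it plans. If both arms are meant, the sentence is misstated and still needs correcting.

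**Bias needs a difference in carriage.** The article speaks of infection and disease risk, never of carriage. Its Discussion expects protection against respiratory infection and diarrhoea to be the most diluted, since children are also infected away from home, and it treats the evidence for benefit on these diseases as uncertain. This stands: a large carriage difference is not established. It does not remove the problem, because sampling one arm makes equal carriage an assumption that cannot be tested.

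**The 44% comes from one chosen pairing.** It halves carriage while holding case prevalence equal. This stands: a reader might take it as the expected bias, but nothing in the document supports that pairing, and the mildest case in the table moves the fraction only from 0.20 to 0.187.

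**The effect on carriage is lost.** A reader might add that the house's effect on carriage cannot be estimated. That is true of this sampling, but carriage is not a listed objective or endpoint, so it is no failing of the plan.

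**Conclusion.** The point holds in conditional form. As the article is written, the novel-arm attributable fraction borrows its background from traditional houses. That fraction, and its comparison between arms, are biased whenever asymptomatic carriage differs by house type. The rationale makes a difference plausible, and the sampling makes it uncheckable.

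Size and direction are unknown. Under the assumptions shown, the error runs from nil (equal carriage) through small (0.187 against 0.20) to large (-0.067 against 0.20).

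A reader might infer that the comparison is certainly biased, that novel-house fractions are necessarily understated, or that the whole microbiology endpoint is lost. The document supports none of these. Equal carriage gives no bias, higher carriage in novel houses reverses the sign, and pathogen frequencies among symptomatic children, swabbed in both arms, can still be compared. The malaria primary endpoint, the respiratory and diarrhoea incidence comparisons and the sample size are untouched. The change should be made, but it concerns one component of one secondary endpoint.

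**What to change.** Change the sampling rule in Methods, Microbiology, so that each asymptomatic swab comes from a child who:

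- lives in the same arm as the symptomatic child;
- lives in a different household, because siblings share pathogens, and a same-house comparator would raise comparator positivity and push the attributable fraction down;
- is of similar age and is swabbed in the same week;
- lives in the same village or a nearby one.

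State in the endpoint section that attributable fractions are calculated within arm before they are compared.

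If control-house-only sampling has already taken place, restrict attributable fractions to control houses and compare only pathogen frequencies among symptomatic children between arms.

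**Cost.** The number of swabs and tests is unchanged, and research assistants already visit every child weekly. There are 110 novel houses in 60 villages, about 1.8 per village (110/60) and at most three, so a matched child from another novel house may have to come from a neighbouring village. With about 330 of 1,650 children in novel houses, roughly one fifth of healthy swabs would move to that arm if symptomatic episodes were equally frequent in both. The novel-arm background would then rest on a fairly small sample, and the control-arm background on about four fifths of the swabs it would otherwise have.
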